Clinical studies with topiramate suggest that it is effective as monotherapy or adjunctive therapy in PTSD. Two open-label studies demonstrated topiramate to be effective and to have a rapid onset of action. Berlant and van Kammen [27] have reported that topiramate decreased nightmares in 79% and flashbacks in 86% of civilian patients with chronic PTSD with improvement of nightmares in 50% and of intrusions in 54% of patients with these symptoms. A partial response was reported for 95% of patients at a dosage of 75 mg/day or less and in 91% of full responders at a dosage of 100 mg/day or less. The nonhallucinatory subgroup achieved a higher response rate (89%). In a prospective open-label study, Berlant [28] treated thirty three civilians with chronic PTSD, with topiramate as monotherapy or augmentation therapy. The PTSD Checklist-Civilian Version (PCL-C) total symptoms declined by 49% at 4th week, with similar subscale reductions for reexperiencing, avoidance/numbing, and hyperarousal symptoms. Topiramate suppressed nightmares in 79% and decreased symptoms of intrusions in 94% in those patients with these symptoms. There is only one double-blind, placebo- controlled study of topiramate as a monotherapy in PTSD. Tucker [29] conducted a 12-week, double-blind, placebo-controlled evaluation of topiramate as a monotherapy in thirty eight civilian PTSD patients. Patients in the topiramate group exhibited significant reductions in reexperiencing symptoms (CAPS cluster B: topiramate = 74.9%; placebo = 50.2%; p = .038) and reductions approaching statistical significance, based on a nominal p value, were noted in mean total Clinical Global Impressions-Improvement Scale scores (topiramate = 1.9 ± 1.2; placebo = 2.6 ± 1.1; p = .055). Although there was a reduction in total Clinician-Administered PTSD Scale (CAPS) score from baseline (topiramate = -52.7; placebo = -42.0), the difference was not statistically significant (p = .232). But not all studies found positive results, Lindley [30] in a double-blind, placebo-controlled study using topiramate as an augmentation therapy in forty male veterans with PTSD did not find significant treatment effects versus placebo. However, there was a high dropout rate from the study with 11 (55%) topiramate and 5 (25%) placebo subjects not completing the seven week treatment, with 40% of topiramate and 10% of placebo dropping because of adverse effects. Patients in the topiramate group that completed the study, had a significant improvement in the reexperiencing subscale of the CAPS suggesting efficacy for the patients that continued the medication.

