#### Active treatment phase

Those patients without improvement during the placebo trial, and do not show any laboratory and clinical condition exclusion criteria will be randomly assigned to receive either placebo or topiramate, in a 1:1 ratio using computer- generated code. The active and placebo pills will be identical. All research and clinical staff will be blinded to the randomized assignments.

Study medication will start at 25 mg/day once daily, at night, and will be increased 25 mg weekly, as tolerated, until complete or nearly complete efficacy is achieved or until 200 mg/day is reached. No other psychotropic medications will be allowed during the study, except for zolpidem (10 mg/day), if needed, for insomnia.

Study follow-up visits will be conducted at baseline, and weeks 1, 2, 3, 4, 6, 8, and 12.

Symptoms and side effects will be assessed, as well as measurement of systemic blood pressure and pulse rate in each visit by the investigator, who is blind to medication assignment. Compliance will be assessed by counting the amount of pills left in the bottle of medicine in each visit.

Treatment will be continued for 12 weeks (active treatment phase); then drug administration will be withdrawn gradually during 2 weeks with reductions of 25/50 mg every three days, according to the final dosage reached.

Patients will be assessed until completing 6 months during a follow-up period. If a patient showed a symptomatology worsening during the active treatment phase (12 weeks) when receiving active drug treatment, characterized by a one-point decrease at CGI -I or present serious adverse effects related to medication, he/she will be excluded from the study.

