Efficacy analyses will be performed in the intent-to-treat population of patients who received at least one dose of topiramate. The primary efficacy endpoint will be the change in PTSD Scale- CAPS total score from baseline to the final visit at 12 weeks, which will be compared between treatment groups. Missing efficacy data at 12 weeks will be imputed with the last observation carried forward. The secondary outcomes between groups will be comparing the Clinical Global Impressions (CGI), the Beck Depression Inventory (BDI), the Global Assessment of Function (GAF), and the PANAS scales. Other secondary analyses will include an evaluation after 24-weeks (12-week after last patient visit with drug) data with endpoint analyses between the treatment groups covarying for baseline scores. On all secondary outcomes, the Bonferroni correction will be applied for testing multiple variables. Response will be defined as a 20% improvement in the baseline CAPS total or positive symptom scores at 12 weeks and will be compared between treatment groups using a chi-square test. Proportions of patients completing the 12-week double-blind study will be compared between treatment groups using a chi-square test. Adverse events reported by 10% of patients in each treatment group will be compared using a chi-square test. Laboratory values, vital signs and physical examinations are going to be compared from baseline and in reference to normal ranges, and reported as normal or abnormal. Changes in body weight (lb), body mass index (BMI; kg/m2) at last visit in the 12-week dataset will be compared as mean changes between treatment groups using t-tests.

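### Last-visit weight change and crude adverse-event proportions ignore time observed, so harms on topiramate would be understated if patients leave earlier or more often in that arm

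*Protocol article*

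**What the plan says.** The Statistical Analysis section of the protocol article fixes two harm comparisons. For adverse events: "Adverse events reported by 10% of patients in each treatment group will be compared using a chi-square test". For body weight and BMI, the change "at last visit in the 12-week dataset will be compared as mean changes between treatment groups using t-tests". Neither uses the time for which a patient was observed.

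The Active treatment phase section sets the data collection: "Symptoms and side effects will be assessed, as well as measurement of systemic blood pressure and pulse rate in each visit". Weight is not named there; it is named only among the screening measurements. The same section says that patients who "present serious adverse effects related to medication, he/she will be excluded from the study", and it applies the same consequence to patients who worsen "when receiving active drug treatment, characterized by a one-point decrease at CGI -I". The sentence just before that rule reads: "Patients will be assessed until completing 6 months during a follow-up period". It does not say whether excluded patients are covered.

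Tolerability is the second aim. The Aims of the Study section measures it by the dropout rate in each group, and the Statistical Analysis section compares completion between arms by chi-square. The Background section describes a seven-week augmentation trial of topiramate in which 55% on topiramate and 25% on placebo did not complete, "with 40% of topiramate and 10% of placebo dropping because of adverse effects".

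**The concern.** A last-visit comparison averages a two-week weight change in one patient with a 12-week change in another as if they were the same quantity. A crude adverse-event proportion counts a patient who left at week 2 as fully observed. Both are harmless if the two arms are observed for similar lengths of time. They are not if exits differ by arm, and one reason for exit here is itself a medication-related harm.

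If topiramate patients leave sooner or in larger numbers, later events are missed more often in that arm, and a weight change that builds over time is diluted there. The dose is titrated upward in weekly steps, so early leavers also contribute no observation at the higher doses. The tables would then show fewer adverse events and a smaller weight change on topiramate than 12 weeks of observation would have shown.

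**Working it through.** The plan gives no figure for harms and no expected dropout by arm, so there is nothing of its own to reproduce. The check shows how far the stated methods could mislead under declared assumptions.

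**Inputs.** From the protocol article: a 12-week treatment period, 36 patients per arm, and the cited trial's non-completion of 55% v 25% and adverse-effect dropout of 40% v 10%. Assumed: these proportions apply over 12 weeks here, observation stops at exit, and exit is independent of the event being counted. The true event risks are illustrative.

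**Model A: uniform leaving times, constant event hazard.** With dropout fraction d and true 12-week risk p, let λ = −ln(1−p). Then

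observed risk = (1−d)·p + d·[1 − (1−e^(−λ))/λ], and share of observation lost = d/2.

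- Observation lost: 0.55/2 = 27.5% v 0.25/2 = 12.5%. Person-weeks: 36×12×0.725 = 313 v 36×12×0.875 = 378, a ratio of 0.83.
- Equal true risk of 30% (λ = 0.357): 22.2% on topiramate v 26.5% on placebo.
- True 50% v 20%: observed 37.8% v 17.6%, so a 30-point excess shows as 20 points.
- Using only the 40% v 10% adverse-effect dropout: 20% v 5% of observation lost, and the 30-point excess shows as 22 points.
- A weight change linear in time is understated by d/2, that is 27.5% on topiramate and 12.5% on placebo.
- If all 55% left in the last third of the period, topiramate would lose 0.55×1/6 = 9%; if all left in the first third, 0.55×5/6 = 46%.

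**Model B: exponential leaving times, as a cross-check.** With k = −ln(1−d)/12 and h = −ln(1−p)/12,

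observed risk = h/(h+k)·(1−e^(−12(h+k))), and mean time observed = (1−e^(−12k))/k.

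- At 55% v 25%: mean time observed is 8.27 v 10.43 weeks (ratio 0.79). A linear weight change appears at 8.27/12 = 69% of its 12-week size on topiramate and 10.43/12 = 87% on placebo.

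Equal true 30% risk under Model B:

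| Dropout, topiramate v placebo | Observed risk | Risk ratio |
|---|---|---|
| 55% v 25% | 21.2% v 26.3% | 0.80 |
| 40% v 10% | 23.8% v 28.6% | 0.83 |
| 30% v 20% | 25.5% v 27.1% | 0.94 |
| 25% v 25% | 26.3% v 26.3% | 1.00 |
| 25% v 55% | 26.3% v 21.2% | 1.24 |

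**Early events.** If all event risk falls in weeks 0 to 4, replace 12 by 4 in the hazard and in the event window, and keep k as above. At 55% v 25% and an equal 30% risk, the result is 26.5% v 28.7%, a ratio of 0.93. Events per person-week of total exposure would give (0.265/8.27)/(0.287/10.43) = 1.17, a larger error in the other direction.

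**The case against.** A reader might infer that the harm comparison *is* biased in favour of topiramate because exclusion ends observation, earlier and more often in that arm. The documents do not support that, for these reasons:

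- The only differential dropout figures come from one cited trial: seven weeks, augmentation, male veterans. This trial lasts 12 weeks and allows no other psychotropic drug except zolpidem. The article gives no leaving times for the cited trial, so nothing supports "earlier".
- The six-month assessment sentence leaves open whether excluded patients are still observed.
- The worsening rule mentions active drug, but staff are blinded and could not knowingly apply it to one arm. If topiramate works as hypothesised, worsening would be commoner on placebo, which pushes the bias the other way.
- The stated measure of the second aim is dropout itself, so differential exclusion would appear openly as worse tolerability.
- The event that triggers exclusion is already counted; only later or different events are lost. The models treat leaving as independent of events, which simplifies the stated mechanism.
- In the equal-risk case the shift is 26.5 − 22.2 = 4.3 points, about 1.5 patients in 36, against a standard error of about 10 points: √(0.222×0.778/36 + 0.265×0.735/36) = 0.10.

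All of this stands. It makes the direction conditional and argues against replacing crude risk with person-time rates. It does not rescue the last-visit t-test, which mixes changes over different durations whichever arm loses more patients. Nor does the separate completion test help: it shows that patients left, but does not correct estimates distorted by their leaving.

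**Conclusion.** The point holds in conditional form. Two stated methods ignore time observed, and the protocol does not settle whether harm data continue after exclusion. If exits are earlier or more frequent on topiramate, harms there are understated. At the cited trial's 55% v 25%, an equal true risk would show as a ratio of about 0.8, and a linear weight change on topiramate would lose roughly 28% to 31% of its size. These sizes rest on borrowed dropout, observation stopping at exit, and constant hazard. The bias is nil with equal exits, small with early events, and reversed if placebo patients leave more.

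The weight and BMI analysis is the firmer part, because its estimand depends on when each patient happened to leave. Understating a weight change makes topiramate look safer only if that change is regarded as a harm. The article reports it alongside the safety measures but does not classify it.

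**What to change.** 1. **Weight and BMI.** In the Statistical Analysis section, replace the last-visit t-tests with a week-12 comparison adjusted for baseline. Use a repeated-measures model on all weights recorded at scheduled visits, or ANCOVA if weight is taken only at baseline and at the end. State at which visits weight is measured, because the Active treatment phase section names only blood pressure and pulse at each visit.
2. **Adverse events.** Keep the crude percentages and chi-square test. Report exposure time by arm, and add time to first event as a sensitivity analysis, not as a replacement. Censoring at a harm-driven exit is informative, and person-week rates can mislead when events come early.
3. **Data collection.** Reconcile the exclusion rule with the six-month assessment sentence. Separate stopping study drug from leaving data collection, so that adverse events and weight are still recorded at the scheduled visits to week 12, by the same rule in both arms. This concerns which data are recorded, not when treatment should stop.

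Cost: no additional patients. Patients who stop study drug are asked to attend visits already scheduled, and there is slightly more analysis work. If weight is not now taken at those visits, recording it is a small addition.
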